### Biochemical and Blood Pressure Assessments

During pregnancy, fasting blood samples will be obtained from the mother twice, in the first and third trimester to assess maternal micronutrient status. The blood samples will be collected by a certified phlebotomist into appropriate test tubes (with or without ethylenediaminetetraacetic acid (EDTA) appropriate for the biomarker to be analyzed. Iceboxes will be used to store the test tubes temporarily until ultimate centrifugation and analysis. The following are the biomarkers that will be examined and with corresponding analytical method:

-Hemoglobin (HemoCue^®^ Glucose 201 + System)-Ferritin (Electrochemiluminescent assay, RocheCobas E 411; Roche Diagnostics, Indianapolis, IN, United States)-Folate (Electrochemiluminescent assay, Roche Cobas E 411)-Vitamin B12 (Electrochemiluminescent assay, Roche Cobas E 411)-Vitamin A (High-Performance Liquid Chromatography)-Vitamin D (Electrochemiluminescent assay, Roche Cobas E 411)-Lead [Inductive Captured Plasma (ICP)]-Zinc [Inductive Captured Plasma (ICP)]

Blood pressure will be measured with a validated and calibrated digital automated sphygmomanometer (Omor Hem-907, Omron Healthcare, Kyoto, Japan) with participants seated after a 5-min rest. These measurements will be obtained at the three visits during pregnancy.

#### Delivery and Birth Outcome Data

Delivery and birth outcome data will be obtained from the records of the hospital at which the birth takes place with the participant’s consent. The data includes occurrence of complications during pregnancy, date and method of delivery, gestational age, sex of newborn, birthweight, length, and head circumference all of which will be measured by a trained researcher or clinician.

### Reliability of Data Collection

The questionnaires to be used in the study were reviewed by the experts in the field. Additionally, the validity of questionnaires will be tested using a pilot group of the study population, however, the FFQ and IPAQ have been validated and used in the UAE population in recent studies (51, 52). Considering that the data will be collected by trained research assistants across the different states of the UAE, several quality assurance activities will be implemented to ensure consistency and reliability standards of the collected information. The principal investigators have compiled a data collection training program with a certification process and detailed operations manual describing the procedures before, during and after data collection to be given to each research assistant. The manual will contain checklists to be followed before and after each visit, including a section on Frequently Asked Questions (FAQs). The instruments used in data collection were carefully chosen and will be identical in each of the facilities where data will be collected, such as measuring tapes, stadiometers, scales, etc. Additionally, there will be regular meetings between the principal investigators and personnel involved in data collection in which probing and interviewing techniques will be standardized to minimize interviewer bias. The principal investigators will regularly visit participating healthcare centers to observe data collection activities, discuss emerging situations and ensure that all procedures are standardized.

### Statistical Analysis and Sample Size Calculation

The data collected will be checked for accuracy and completeness and will be entered into the Statistical Package for Social Science (SPSS) software, using the most current version. The primary aim of the study is to examine the associations between maternal nutrition (e.g., weight gain, micronutrient status, etc.) and infant health outcomes (e.g., growth rate, dietary diversity score, feeding practice score, etc.). Given the somewhat limited data on the above-mentioned relationships, for power calculation an *r* = | 0.2| was chosen, as it yields the largest sample size. Using the UCSF sample size calculator, the sample size needed to detect a correlation as small as | 0.2|, at 80% power and 5% type I error, is determined at 194. For this study, correlations less than 0.20 would be too small to be considered clinically significant (37). Given the high attrition rate seen in previous birth cohorts (37), we estimate that roughly 15% of the participants will drop out after the first visit. An additional 10% was factored into for losses due to preterm delivery or still birth. More participants (∼10% of sample) are also required to test for simple interactions in our study (e.g., Emirati, Sex, and Timing). Thus, the original sample size was increased by 35% and the intended sample size was determined at 260 pregnant women.

Frequencies and percentages will be used to describe categorical variables and mean, and standard deviations will be used to describe continuous variables. The chi-square test (χ2) or Fisher’ s exact test will be used to calculate the association between categorical variables. Independent *t*-tests and Mann-Whitney tests will be used to chart comparisons for normal and non-normal continuous variables, with normality of variables evaluated using the Kolmogorov-Smirnov and Shapiro-Wilk tests. Associations among the variables of the cohort study (i.e., maternal factors, birth outcomes, breastfeeding, complementary feeding, growth patterns, etc.) will be examined using simple linear and logistic regressions. The two main dependent variables in this study are related to birth outcomes and growth patterns of the child. Variables showing statistical significance in the univariate analysis will be included in the multivariate models as covariate factors in order to control for potentially confounding variables that have been used in the model. Parameter estimates and their respective 95% confidence intervals will be calculated for linear regression analyses, whilst for logistic regression analyses odds ratios and their respective 95% confidence intervals will be calculated. Tests for linearity (tolerance > 0.4) of the covariates included in the regression models will be performed. Normality of the residuals will be assessed using the histogram of standardized residuals and normal probability plot in all linear regression models. *P*-values less than 0.05 will be considered to indicate statistical significance.

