### Study Participants

The study aims to recruit a total of 260 pregnant Emirati females during their first trimester (8–12 weeks of gestation) through face-to-face recruitment at OB-GYN clinics in selected health care facilities across the Emirates of the UAE. The participants will be provided with both verbal and written information (Participant Information sheet) about the study aims, data collection activities, and duration of the study. Mothers will consent to the study on behalf of their children to be included in the study, by signing a form, after meeting the following inclusion and exclusion criteria.

Inclusion Criteria:

•Emirati Nationality•Within first trimester of pregnancy (between 8–12 weeks of gestation)•Singleton pregnancy•Absence of major illness preconception (Diabetes mellitus, hypertension, kidney disease, cancer, epilepsy, severe psychiatric illness, and other chronic diseases of infections such as autoimmune disorders, human immunodeficiency virus, and hepatitis).

Exclusion Criteria:

•Non-Emirati Nationality•Unconfirmed viable, intrauterine pregnancy at first obstetric ultrasound during first trimester•Twin or multiple gestation pregnancy and a history of multiple gestations•History of chronic illness (i.e., T2DM, hypertension, etc.)•Previously given birth to babies with malformation, intellectual disability, or inborn errors of metabolism.•Experience of a miscarriage before 28 weeks of gestation•Use of significant regular medications, including insulin, anti-hypertensive agents, psychotropic medications, anti-epileptic drugs, steroids, immune-suppressive agents, and chemotherapeutic agents.

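### The 35% increase to 260 is almost entirely used up by the stated losses, so the roughly 10% allowance for interaction tests is not there; one named interaction factor, Emirati, cannot vary in this cohort

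*Protocol article*

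**What the plan says.** All figures are in the protocol article, section Statistical Analysis and Sample Size Calculation. The base number, for a correlation of 0.2 "at 80% power and 5% type I error, is determined at 194". Three additions follow:

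- Dropout: "we estimate that roughly 15% of the participants will drop out after the first visit".
- Pregnancy-related losses: "An additional 10% was factored into for losses due to preterm delivery or still birth".
- Interactions: further participants, about 10% of the sample, "are also required to test for simple interactions in our study (e.g., Emirati, Sex, and Timing").

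The conclusion is: "Thus, the original sample size was increased by 35% and the intended sample size was determined at 260 pregnant women".

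Two other sections bear on the interaction factors. Study Participants requires Emirati nationality and lists "Non-Emirati Nationality" as an exclusion. Study Design divides the country into three recruitment areas (Abu Dhabi, Dubai and the Northern Emirates), with about 40%, 30% and 30% of participants.

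**The concern.** The three percentages do different jobs but are handled alike. The interaction allowance is an addition to the number needed for analysis. The two losses are fractions of the women enrolled, so the analysis number must be divided by the fraction retained. Treating a loss as an addition understates the enrolment it requires, and the shortfall has to come out of something. Here it comes out of the share set aside for interactions.

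At stake is what readers may take 260 to provide. The text presents the total as including extra women for interaction tests. If those women are not there, an inconclusive interaction result could be given more weight than it deserves. Separately, a factor with one level in the cohort cannot interact with anything, so the list of factors as printed cannot be carried out.

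**Working it through.** **Inputs.** From Statistical Analysis and Sample Size Calculation: r = 0.2, 80% power, 5% type I error, base 194, losses of 15% and 10%, interaction allowance of about 10%, total 260. Sidedness is not stated; two-sided is used because it reproduces 194.

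**1. The plan's own figures.**
- Base, by Fisher's z: n = ((1.960 + 0.8416) / atanh(0.2))² + 3 = 193.97, so **194**. It reproduces.
- Inflation: 15% + 10% + 10% = 35%, and 194 × 1.35 = 261.9. The stated 260 is 260/194 = 1.34 times the base, which agrees within rounding.

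**2. Enrolment needed for the losses alone.**
- Losses added (25%): 194 / 0.75 = 258.7, so **259**.
- Losses in sequence: 194 / (0.85 × 0.90) = 194 / 0.765 = 253.6, so **254**.

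**3. What 260 delivers.** Power for one correlation is Φ(atanh(0.2) × √(n − 3) − 1.960).

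| Losses | Analysable | Above 194 | Power at r = 0.2 |
|---|---|---|---|
| Added | 260 × 0.75 = 195 | 1 (0.5%) | 80.2% |
| In sequence | 260 × 0.765 = 198.9, about 199 | 5 (2.5%) | 81.0% |

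The stated allowance is 10% of 194 = 19.4, about 20 women.

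**4. Enrolment that would deliver the allowance.**
- 10% of the base: 194 × 1.10 = 213.4, so 214 analysable. Then 214 / 0.75 gives 286, and 214 / 0.765 gives 280.
- 10% of those enrolled: 194 / 0.75 / 0.90 gives 288, and 194 / 0.765 / 0.90 gives 282.

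The range is **280 to 288**, against 260.

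**5. What the allowance would have bought.** The protocol gives no interaction effect size, so this is an illustration: a correlation of 0.2 in one sex and 0 in the other, with two equal, independent halves. The difference on the Fisher-z scale is 0.2027, with standard error √(2 / (n/2 − 3)).
- n = 195: SE = √(2/94.5) = 0.1455; power = Φ(0.2027/0.1455 − 1.960) = **29%**.
- n = 214: SE = √(2/104) = 0.1387; power = Φ(0.2027/0.1387 − 1.960) = **31%**.
- Difference detectable with 80% power at n = 195: 2.8016 × 0.1455 = **0.41** on the Fisher-z scale. For scale, r = +0.2 against −0.2 is a difference of 2 × 0.2027 = 0.405.

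**6. The factor Emirati.** Every participant must be Emirati, so the factor has a single level. Emirate or region has three levels in Study Design and would fit beside sex and timing.

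**The case against.** The strongest reply is that little depends on this. Power for the main association stays at 80% or slightly above, and 260 need not change. Delivering the whole allowance would move the illustrative interaction power only from 29% to 31%. The article promises no power for any interaction, and its analysis paragraphs set out no interaction model. All of this stands. It limits the size of the point, but it does not make the stated composition of 260 correct.

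A second reply is that some margin may remain. With losses in sequence, 5 women are left. Preterm deliveries also need not be lost to the birth-outcome analyses, since preterm birth and gestational age are themselves recorded. Both are fair. On the plan's own losses, however, neither way of combining them leaves anything near 10%.

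A reader might infer more than the documents support:

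- *That 260 is too small for the primary association.* It is not, under the stated losses.
- *That 260 is a miscalculation of 262.* With inputs given as rough percentages, this is rounding.
- *That choosing 0.2 because it yields the largest sample is false.* The same paragraph treats smaller correlations as not clinically significant. Among values of 0.2 and above, 0.2 does need the most women.
- *That miscarriage is left out of the loss budget.* The documents give no rate, and the 15% dropout after a first visit at 8 to 12 weeks may include it. The eligibility item "Experience of a miscarriage before 28 weeks of gestation" is an exclusion criterion and says nothing about the budget.
- *That 0.41 also applies to timing.* Timing is not defined. If it means visit or trimester, the measurements are repeated in the same women and the two-group formula does not apply.

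**Conclusion.** The point holds as a misstatement of what 260 contains. After the stated losses, 195 to 199 women are analysable, so the interaction allowance is 1 to 5 women and not about 20. This rests only on the plan's own percentages and holds whether the losses are added or taken in sequence. The base of 194 and the 80% power for one correlation of 0.2 are sound, so the consequence is confined to the interaction claim. The interaction power figures depend on an assumed effect (0.2 versus 0) and equal sex groups, and serve only to show scale.

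Emirati as printed cannot be an interaction factor under the eligibility criteria. The three recruitment areas make a slip for Emirate likely, but the text does not settle it, so the sponsor should say what was meant.

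**What to change.** Keep 260 and change the text of the sample size section:

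1. State that, under the stated losses, 260 enrolled gives 195 to 199 analysable women and 80% to 81% power for one correlation of 0.2.
2. Withdraw the statement that the total includes about 10% for interactions.
3. Label interaction tests exploratory and report them as estimates with 95% confidence intervals. For sex, give the detectable difference of about 0.41 on the Fisher-z scale at n = 195.
4. Replace Emirati with the intended factor, for example region, or remove it.

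The cost is wording only, and the stated capability becomes slightly less favourable. The alternative of delivering the allowance would mean enrolling 280 to 288, that is 20 to 28 more women, for about two percentage points of power in the illustrative sex interaction. That is hard to justify.

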#### During Pregnancy

Pregnant females will be recruited during their first trimester (8–12 weeks of gestation) in OB-GYN clinics and perinatal health facilities in the UAE. There will be one visit during each trimester of pregnancy, and an additional eight visits postpartum. The initial prenatal assessment screening will aim to measure key factors such as diet and supplement use, physical activity and lifestyle practices, maternal psychological, sociodemographic, and socioeconomic characteristics, through anthropometric measurements and validated questionnaires. Blood samples will be collected from participants during the first and third trimester for biochemical analysis of several biomarkers. Maternal exposure, knowledge, attitudes, and intention toward infant feeding practices will be assessed during the third trimester through questionnaires. Information on fetal growth from ultrasound will be collected during the second and third trimester.

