#### Post-partum

The participants’ hospital records will be used to obtain information about the delivery, as well as birth outcomes data. Postnatal visits will take place when the child is 0.5, 4, 6, 9, 12, 18, and 24 months old. These visits will consist of anthropometric measurements and assessment of child feeding practices (breastfeeding and complementary feeding practices, dietary intake, supplement use, and the eating environment at home). Developmental assessments will take place at three points: (a) within 2 weeks of birth, (b) at 10–14 months, and (c) at 22–26 months of age. In addition, the mothers will undergo postpartum assessment at each postnatal visit. This will consist of anthropometric measurements, collection of dietary intake data, supplement use, lifestyle habits, physical activity, and psychological state.

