#### Anthropometric Assessment of Infants and Young Children

Anthropometric assessment of infants and young children will be taken at each of the six visits after birth and will include measurement of weight, length, head circumference and mid-upper arm circumference (MUAC). Anthropometric measurement protocols and quality control procedures will follow the WHO MGRS INTERGROWTH-21st Project protocol (40–42). Study equipment will include portable electronic weighing scales (Seca model 376; Seca, Hangzhou, China); recumbent length will be measured using a Harpenden Infantometer (range 300–1,100 mm; Chasmors Ltd., London, United Kingdom), flat metal tape measure will be used for head circumference measurement (CMS ref.3105; Chasmors Ltd., London, United Kingdom). MUAC will be measured using a tape around the arm at the level of the midpoint (42).

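### Repeated infant growth measurements are assigned to ordinary regression with no time point or per-child summary defined, and the number of infant measurement visits is inconsistent

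*Protocol article*

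**What the plan says.** All references are to the Protocol article.

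**Analysis.** In Statistical Analysis and Sample Size Calculation, the outcomes are introduced with "The two main dependent variables in this study are related to birth outcomes and growth patterns of the child". The method for associations among the cohort variables is given as "complementary feeding, growth patterns, etc.) will be examined using simple linear and logistic regressions". The next step is: "Variables showing statistical significance in the univariate analysis will be included in the multivariate models as covariate factors". Group comparisons use independent t-tests or Mann-Whitney tests. No method for repeated measurements is named. The same section mentions growth rate, but only as an example of an infant outcome.

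**Measurement schedule.** During Pregnancy states: "There will be one visit during each trimester of pregnancy, and an additional eight visits postpartum". This agrees with the total of 11 visits in Study Protocol. Post-partum states: "Postnatal visits will take place when the child is 0.5, 4, 6, 9, 12, 18, and 24 months old", and continues: "These visits will consist of anthropometric measurements and assessment of child feeding practices". Anthropometric Assessment of Infants and Young Children states: "Anthropometric assessment of infants and young children will be taken at each of the six visits after birth". The abstract (Methods/Design) gives both the eight visits after delivery and the seven ages.

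**The concern.** A growth pattern is seen only across several measurements of one child. Linear regression, logistic regression and the independent-sample tests all assume one independent observation per unit. The section therefore assigns to a main outcome a method that does not fit the data as collected. It also omits the definition (a time point, or a growth summary per child) that would make the method fit.

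The analyst can then proceed in three ways: pool the visits, run one regression per visit, or reduce each child to one number. These differ in validity and in the question they answer, and the text does not choose between them. The choice could be made after the data are seen.

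The conflicting visit counts add to this, because the number of growth measurements per child is itself not settled.

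**Working it through.** **1. The plan's own figure.** Inputs from the sample size section: correlation 0.2, power 80%, type I error 5% (taken as two-sided).

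n = ((1.960 + 0.842) / atanh(0.2))² + 3 = 193.97, so 194, as stated. Increasing by 35%: 194 × 1.35 = 261.9, against the stated 260. This calculation uses one pair of values per participant, so it does not depend on how many visits each child has.

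**2. If visits were pooled.** The number of visits per child, m, is 6 or 7 (from the two sections on infant measurement). The within-child correlation ρ is not given in the article. It is assumed here to be exchangeable, over the range 0.3 to 0.9. The exposure is taken as constant within the child, such as first-trimester micronutrient status.

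- Design effect: D = 1 + (m − 1)ρ
- Reported standard error relative to the true one: 1/√D
- Actual type I error of a nominal 5% test: 2(1 − Φ(1.96/√D))

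| m | ρ | D | SE ratio | Type I error |
|---|---|---|---|---|
| 6 | 0.3 | 2.5 | 0.632 | 21.5% |
| 6 | 0.5 | 3.5 | 0.535 | 29.5% |
| 6 | 0.8 | 5.0 | 0.447 | 38.1% |
| 6 | 0.9 | 5.5 | 0.426 | 40.3% |
| 7 | 0.3 | 2.8 | 0.598 | 24.1% |
| 7 | 0.5 | 4.0 | 0.500 | 32.7% |
| 7 | 0.8 | 5.8 | 0.415 | 41.6% |
| 7 | 0.9 | 6.4 | 0.395 | 43.8% |

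A simulation with 194 children and 4,000 runs per setting agrees: 29.7% and 39.5% for six visits, and 33.1% and 42.1% for seven, at ρ = 0.5 and 0.8.

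**3. If each visit is analysed separately.** Independence holds within each regression. If all four measures (weight, length, head circumference, arm circumference) were tested at every visit, there would be 4 × 6 = 24 or 4 × 7 = 28 tests per exposure. For one measure, the chance of at least one false positive would be 1 − 0.95⁶ = 26.5% or 1 − 0.95⁷ = 30.2% if the tests were independent, and less for positively correlated visits. No trajectory is estimated, and a child who misses a visit is lost from that visit's analysis. The sample size section itself expects about 15% dropout.

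**4. If each child gives one value.** Ordinary regression is valid. In the same simulation, using each child's mean, the type I error was 4.9% to 5.8%.

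**5. Visit counts.**

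- During Pregnancy and the abstract: eight postpartum visits (11 − 3 = 8).
- Post-partum and the abstract: seven ages; Post-partum says these visits include anthropometry.
- Anthropometric Assessment of Infants and Young Children: six visits.

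Counting delivery as a visit could turn seven into eight, though the text does not say so. It cannot turn seven into six.

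**The case against.** The strongest reply is that nothing in the article commits to pooling. The growth-rate example is naturally one value per child, and the sample size is for a single correlation with one pair per participant. Under that reading, ordinary regression is correct. This stands. A reader might infer that the plan will analyse all visits as independent and so carry a type I error of 33% to 42% (seven visits, ρ of 0.5 to 0.8). The documents do not support that inference: the arithmetic is right, but both the pooling and the correlation are assumptions.

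A reader might also infer that only one-predictor regression is planned. That is not so: simple regression is the screening step and multivariable models follow. However, adding covariates does not account for repeated measurements on a child.

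It can also be said that an article leaves such detail to the full protocol or SAP. That has force for the exact growth definition. It has less force for the method, because the article does choose one, including residual diagnostics for the linear models, and applies it by name to growth patterns.

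On the counts, the timeline figure is not shown, and staff will work from an operations manual with visit checklists (Reliability of Data Collection). It is therefore not established that any site would omit a measurement. The conflict between six and seven in the text remains.

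**Conclusion.** The point holds in a limited form. For a main dependent variable measured six or seven times per child, the article names only methods for independent observations. It does not fix the time point or per-child summary under which they would be adequate.

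The size depends on the reading. With pooled visits, the type I error is 21.5% to 43.8% and reported standard errors are 0.63 to 0.40 of their true size, given ρ of 0.3 to 0.9, exchangeability and an exposure constant within the child. With separate visits there is no such error, but there are up to 24 or 28 tests per exposure and no estimate of growth over time. With one value per child there is no error, but the value is undefined.

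The visit-count conflict is a plain inconsistency. Six against seven cannot be resolved from the text, and eight against seven only by an assumption that the text does not make.

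**What to change.** Define the growth outcome for each measure, for example as age- and sex-standardised z-scores. Then do one of the following:

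- **Use all available visits.** Fit a linear mixed model with the child as the random unit and an exposure-by-age term as the effect on growth. For binary growth outcomes, use GEE or a mixed logistic model clustered on the child.
- **Keep ordinary regression.** Prespecify one time point or one summary per child (with its measure, interval and formula) as the outcome.

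Either resolves the analysis point. The first uses the collected data more fully and keeps children with missed visits. The cost is wording and modest analyst time, with no new data and no change to the 194 or 260.

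Separately, reconcile the abstract, Study Protocol, During Pregnancy, Post-partum, and Anthropometric Assessment of Infants and Young Children, so that all give the same number and ages of infant measurement visits. State whether delivery counts as a visit.
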